## Abstract

**Introduction::**

Chuna manual therapy (CMT) is a type of manual medicine practiced by Korean medical doctors in South Korea. Spinal diagnosis in CMT uses a system that applies manual diagnostic and X-ray tests to detect specific vertebral malpositions, based on the relative alignment across vertebral bodies. Recently, artificial intelligence (AI) programs have been developed to assist in the radiological diagnosis of CMT using X-ray images. Nevertheless, a few clinical studies have reported on the concordance between diagnosticians, diagnostics methodologies, and the use of AI programs for diagnosing CMT. At present, the evidence to support CMT diagnosis is insufficient. This study thus aims to overcome such limitations by collecting and comparing CMT diagnostic data from experts and non-experts through manual diagnosis, X-ray test, and images obtained using an AI program. The study aims to search for CMT diagnosis methods with more outstanding rationality and consistency and to explore the potential use of AI-based CMT diagnosis programs.

**Methods/design::**

This study will be conducted as an exploratory, cross-sectional, prospective observational study that will recruit 100 non-specialist subjects. Each subject will submit a signed consent after the screening test and undergo L-spine standing AP & lateral X-ray imaging. Manual CMT diagnosis will be performed by 3 CMT experts according to the standard operation procedure (SOP). The X-ray images of the 100 subjects will subsequently be used to make the CMT radiological diagnoses according to the same SOP by the CMT expert group (n = 3) and CMT non-expert group (n = 3). Among the subjects, those in the non-expert group will receive another CMT radiological diagnosis with spinal data obtained using the AI program, approximately 1 month from after initial diagnosis.

Based on the collected diagnostic data, within- and between-group concordance levels will be assessed for each diagnostic method. The verified level of concordance will be used to test the potential use of CMT diagnostic method and CMT AI programs with high levels of rationality and consistency.

**Ethics and dissemination::**

This trial has received complete ethical approval from the Wonkwang University Korean Medicine Hospital (IRB 2021–8). We intend to submit the results of the trial to a peer-reviewed journal and/or conferences.

**Trial registration::**

https://cris.nih.go.kr/cris/search/detailSearch.do?search_lang=E&search_page=M&pageSize=10&page=undefined&seq=20613&status=5&seq_group=20613, Identifier: KCT0006707.

## Introduction

1

Chuna manual therapy (CMT) is a method of manual therapy practiced by Korean medical doctors (KMDs) through the use of their hands, other body parts, or an assistive tool, such as the Chuna table, to apply an effective stimulation to the patient's body so as to treat a structural or functional problem.^[1]^ CMT was listed in the National Health Insurance Coverage in South Korea in 2019,^[2]^ and since then, valid effects have been reported for various musculoskeletal diseases.^[3,4]^

The spinal diagnosis system in CMT examines the upper vertebral bodies based on their relative position to the lower vertebral bodies, with standard kinetic viewpoints.^[5]^ Such CMT diagnoses most commonly apply a manual diagnosis that locates the spinal bony landmarks in the patient.^[1]^ Recently, to overcome the limitation of manual diagnosis in the evaluation of spinal alignment and improve diagnosis reproducibility, CMT diagnosis methods that use radiological devices, such as X-rays, have attracted increased interest as have other manual medicine methods, including osteopathy and chiropractic.^[6,7]^ In addition, recent attempts to measure spinal angles or diagnose spinal diseases have used artificial intelligence (AI) programs, such as conventional neural networks or deep learning.^[8]^ Positive results have also been reported for the AI programs to detect the lumbar vertebral landmarks in relation to CMT diagnosis.^[9]^

Nevertheless, the clinical evidence for such CMT-based spinal diagnosis methods is insufficient at present. Despite a number of studies that have investigated the concordance in manual medical diagnostic methods including CMT,^[10]^ the lack of adequate levels of evidence or reliability in manual medicine evaluation has been pointed out in systematic reviews of clinical studies on manual medical diagnostic methods regarding nonspecific lumbar pain.^[11]^ Another limitation is the insufficient number of clinical studies regarding CMT diagnosis compared to those regarding other diagnosis methods in manual medicine. Moreover, there is either a general or complete lack of studies on the concordance between diagnosticians, diagnostic devices, and the clinical use of AI programs in CMT diagnoses.

In this study, the concordance between diagnosticians and diagnostics used for each CMT diagnosis method commonly used in clinical practice will be compared to collect evidence to support the best use of CMT diagnosis methods. More effective CMT diagnosis methods will be explored, and the positive effects of CMT AI programs in clinical practice regarding diagnosis concordance and accuracy will be investigated, to provide basic data to test the potential use of AI programs in future clinical CMT applications.

## Objectives

2

In this study, based on the CMT diagnosis of the lumbar spine, 4 diagnosis groups will be constructed;

1.CMT expert group (n = 3) for manual diagnosis;2.CMT expert group (n = 3) for radiological diagnosis;3.CMT non-expert group (n = 3) for X-ray radiological diagnosis;4.CMT non-expert group (n = 3) for AI-based X-ray radiological diagnosis.

The results will be collected for the specific diagnosis performed on the study subjects. Within- and between-group concordance levels will be subsequently compared to search for clinically effective CMT diagnosis methods. The potential use of the AI-based CMT diagnosis program will also be verified.

## Methods

3

### Trial registration

3.1

This study has been registered in the Cris.nih.go.kr (Trial registration number: KCT0006707; protocol version 1.2; https://cris.nih.go.kr/cris/search/detailSearch.do?search_lang=E&search_page=M&pageSize=10&page=undefined&seq=20613&status=5&seq_group=20613).

### Study design

3.2

This study is an exploratory, cross-sectional, prospective observational study. The number of subjects to be recruited is 100, and data from patient enrolment, manual diagnosis by CMT experts, to X-ray imaging are to be collected at the Wonkwang University Korean Medicine Hospital, Iksan, South Korea. CMT diagnostic data obtained from X-ray images are to be collected at the Catholic Kwandong University International St. Mary's Hospital, Incheon, South Korea, where CMT expert and non-expert groups are defined.

The study flow chart and its details are presented in Figure 1. The recruited subjects will be provided with an adequate and detailed explanation on the study, after which they will submit signed consent. The enrolled subjects will visit the study center at least twice. The subjects will undergo screening (visit 1), and after submitting consent, they will be examined to verify whether they are participating in another clinical study and identify their demographics and basic physical data (height, weight, body mass index, and vital signs). Inclusion and exclusion criteria will also be applied. The finally-selected subjects will undergo subsequent steps (visit 2), and after being assigned with an individual registration number, they will receive a basic physical examination, an evaluation of lumbar pain, and an X-ray test (L-spine standing AP & Lateral). Next, the same subjects will undergo a manual CMT diagnosis by each of the 3 CMT experts, and the relevant information will be documented in the case report form (CRF). All subjects will undergo identical diagnoses, without being divided into specific groups. The steps at visit 1 and visit 2 may be performed on identical dates, and of the steps at visit 2, the X-ray test and CMT manual diagnosis (or palpation) may not be performed within a single day, in which case the respective subject will make a third visit within a week from visit 2. After completing all scheduled visits, the subjects will no longer be required to make further visits. The CMT manual diagnosis and X-ray test will be performed once for each subject.

**Figure 1 F1:**
[figure not shown]
Flow chart of the study.

The X-ray images of the 100 subjects collected at the Wonkwang University Korean Medicine Hospital will be anonymized in a DICOM format that removes the subject identification data and then transferred to the Catholic Kwandong University International St. Mary's Hospital. Using these images, the CMT diagnosis will be performed independently by CMT expert and non-expert groups (3 individuals in each group). To prevent learning effects, the CMT non-expert group will perform the radiological diagnosis once more after around a month, using the same X-ray data, but this time, with the assistance of an AI program to define the relative position of the lumbar vertebral bodies for CMT diagnosis.

The investigators responsible for the clinical study, who participate in the process of diagnosis, will comply with the same standard operation procedure (SOP) for each diagnosis method. The diagnosis results collected in this study will be analyzed for within- and between-group concordance levels per diagnosis method.

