**Figure 3 F3:**
[figure not shown]
Example of the feature point locations suggested by the AI program.

The CMT non-experts (n = 3) who perform the radiological diagnosis will once more be provided with the X-ray images, which will be identical to the previous ones, around a month after the initial diagnosis, together with an AI program. They will then use the AI program to perform a CMT radiological diagnosis based on the reference points suggested by the AI program, to assist with the detection of the positions of vertebral bodies in the lumbar spine. The results will all be recorded in the same CRF used in the manual and radiological diagnoses.

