### Recruitment, randomization, blinding, and non-blinding

3.8

The subject recruitment ad will be posted on the hospital notice boards and websites of Wonkwang University Korean Medicine Hospital. All ads to be used in this study will first be approved by the IRB.

This study is an exploratory, cross-sectional, prospective observational study that does not involve randomization or a process related to blinding. However, to prevent evaluation bias, an independent investigator will perform the subject screening, collection of demographic data, and analysis of baseline health and medical history. All investigators in the CMT diagnosis will also be assigned an independent space to perform the evaluations, while any unnecessary talks or contact among different investigators or with subjects will be prevented during the evaluations, so that the investigators cannot acquire knowledge of the diagnosis results of other investigators. The investigators that perform the radiological diagnosis will solely use anonymized X-rays images, while appropriate measures will be applied to prevent the investigators from sharing the diagnosis data among themselves.

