## Discussion

4

The purpose of this clinical study is to compare and collect the evidence of the diagnostic concordance between diagnosticians and the diagnostics most widely used and well-known in CMT. The study has the following advantages: First, among the studies published so far regarding CMT diagnosis, this study proposes a design based on the largest number of cases and diagnosticians. Previous studies either had a very small number of cases or relied solely on a single diagnostician to pose a difficulty in defining sufficient rational evidence of the diagnosis outcomes.^[13]^ Thus, it is anticipated that the present study will provide the basic data for establishing a higher level of evidence in the CMT diagnostic field.

Second, most previous studies on manual diagnoses obtained the diagnoses based on the personal experience of the diagnostician, without an established SOP and compared the outcomes. On the contrary, the diagnosis in this study is performed according to an SOP that was produced using the contents of regular educational courses conducted by all Korean Medicine colleges in South Korea and by the KSCMMSN. The type of diagnoses are also specified based on the respective spinal abnormality, lumbar level with abnormality, and type of abnormality, to allow an in-depth analysis of the items with a high level of diagnostic concordance and those with a low level of concordance. Through this process, the rational diagnostic capabilities of current regular educational courses can be verified. The study will also provide basic data for developing further diagnostics or educational methods for items with a high error rate. In addition, comparing the manual diagnosis results between the CMT expert and non-expert groups is likely to induce additional discussions on methods for improving diagnoses by non-expert groups.

Lastly, the significance of this study lies in its being the first clinical study to apply an AI program in CMT as well as in the field of manual medicine, to the best of our knowledge. For CMT radiological diagnoses assisted by an AI program, the potential use of AI-based CMT diagnosis programs in clinical practice can be tested by determining whether the methodology results in an improvement in diagnostic concordance by CMT non-experts compared to CMT experts.

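### The AI-aided reading always comes second, on the same films and by the same readers, so the change it brings cannot be separated from the effect of a second reading

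*Protocol article*

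**What the plan says.** The order of reading is stated consistently in three places.

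- Abstract, Methods/design: "The X-ray images of the 100 subjects will subsequently be used to make the CMT radiological diagnoses" by experts and non-experts, and the non-experts make a further diagnosis with AI about a month later.
- Section 3.2 (Study design), first reading: "Using these images, the CMT diagnosis will be performed independently by CMT expert and non-expert groups (3 individuals in each group"). Second reading: "To prevent learning effects, the CMT non-expert group will perform the radiological diagnosis once more after around a month, using the same X-ray data". What differs at that reading is that the AI program helps the reader to locate the vertebrae.
- Section 3.7.3 (X-ray test using an AI program): the non-experts who made the first radiological diagnosis receive the films again, "which will be identical to the previous ones, around a month after the initial diagnosis, together with an AI program".

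No unaided second reading is described. Nor is a second radiological reading by the experts, or a separate set of non-experts for the AI condition. Section 3.8 says that the study "does not involve randomization or a process related to blinding"; its safeguards are anonymised images and no sharing of results between investigators.

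The Discussion (Section 4) rests the test of the AI program on "determining whether the methodology results in an improvement in diagnostic concordance by CMT non-experts compared to CMT experts".

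**The concern.** The improvement named in the Discussion is a change between two readings by the same people. Those readings differ in two respects at once: the second has AI, and the second is the second. By then each non-expert has applied the standard procedure to 100 films and has seen these particular films before.

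Section 3.2 recognises the threat and offers the month's interval as the answer. An interval can weaken memory of single films. It does not undo the experience of having worked through 100 films under the procedure.

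At stake is the interpretation of the aided-versus-unaided contrast. A rise in concordance might be credited to AI when it came from practice. A flat result might be read as no benefit when readers were repeating remembered answers.

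**Working it through.** The protocol gives no figure for practice, recall or AI benefit, so there is no figure of the plan's own to reproduce. The check has three parts.

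**1. Can the two effects be separated?**

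Inputs from Sections 3.2 and 3.7.3: 3 readers, 100 films, 2 sessions, so 3 × 100 × 2 = 600 readings. Fit terms for reader (3), film (99 after a reference film), AI (1) and session (1): 104 parameters.

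- In the planned order, AI = 0 throughout session 1 and AI = 1 throughout session 2. The AI and session columns are identical: their correlation is 1.0 and the design matrix has rank 103 for 104 parameters. One effect cannot be estimated.
- If each reader reads half the films with AI first and half unaided first, and swaps at session 2, the correlation is 0.0 and the rank is 104 of 104. The number of readings is unchanged.

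This is a property of the order of reading, so no analysis plan could repair it.

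**2. How large could the confusion be?**

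Everything in this part is hypothetical. Assume a binary item (abnormality present or absent), prevalence 50%, equal accuracy on positives and negatives, errors independent between readers, and no AI effect. For two readers with accuracies a and b:

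- observed agreement = ab + (1 − a)(1 − b)
- chance agreement = 0.5
- kappa = (observed − 0.5) / 0.5 = (2a − 1)(2b − 1)

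With expert accuracy 0.85, 2b − 1 = 0.70. For agreement within the non-expert group, a = b.

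| Non-expert accuracy | Kappa against an expert | Within-group kappa |
|---|---|---|
| 0.75 (session 1) | 0.50 × 0.70 = 0.35 | 0.50² = 0.25 |
| 0.77 | 0.54 × 0.70 = 0.38 | 0.54² = 0.29 |
| 0.80 | 0.60 × 0.70 = 0.42 | 0.60² = 0.36 |
| 0.85 | 0.70 × 0.70 = 0.49 | 0.70² = 0.49 |

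A practice gain of 2, 5 or 10 points thus appears as a within-group gain of 0.04, 0.11 or 0.24, and as a gain against experts of 0.03, 0.07 or 0.14. A simulation under the same assumptions (3,000 runs, 100 films, 3 readers) gave apparent gains in Fleiss' kappa of about 0.04, 0.11 and 0.24, and about 0.00 when there was no practice gain.

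Recall is not in this model. If readers repeat remembered answers, the second reading is pulled toward the first and a true AI change shrinks.

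**3. Does a swapped order with a common split remove the problem?**

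Let sets A and B hold 50 films each, with the same split for all three readers. Write each cell's kappa as a set term (k_A or k_B), plus p in session 2, plus d if AI is used.

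- Session 1, AI minus unaided: (k_B + d) − k_A
- Session 2, AI minus unaided: (k_A + p + d) − (k_B + p)
- Average of the two: d

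An additive session effect p and any difference between the sets both cancel. Because the split is the same for all readers, every reading of a film within a cell comes from one session, so Fleiss' kappa does not mix sessions.

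**The case against.** **The interval is a genuine safeguard.** A month can be expected to reduce memory of single films. This stands: what can be criticised is the claim of prevention, not the interval itself.

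**Practice may be small.** Section 3.5.2 defines the non-experts as practitioners who already perform this therapy, and no passage gives them correct answers between sessions. This also stands. The accuracies and the prevalence in the table are assumptions, a 2-point gain shifts within-group kappa by only about 0.04, and a binary model fits lumbar level and type of abnormality poorly. But unknown size does not make the contrast identifiable.

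**The study is exploratory.** That excuses imprecision and the absence of a formal sample size. It does not make a contrast interpretable when AI and session coincide.

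**Film order and recoding may be in the full protocol.** Agreed. Their absence from an article is not a defect, and they would not change the order of conditions.

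**Swapping has costs.** Unaided first avoids any carry-over from AI landmarks and keeps all unaided reads in one session. This stands, and the fix has to state it.

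Two stronger readings are tempting. A reader might infer that the bias must favour AI. The documents do not support that, since recall could mask a real change. A reader might also infer that the study's concordance results are compromised as a whole. They are not: the expert manual-versus-radiological comparison and all first-session concordance involve no second reading of a film.

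**Conclusion.** The point holds for the aided-versus-unaided contrast only. With AI second for every reader and film, and no unaided reread, the observed change is the combined effect of AI and a second reading. That conclusion needs no numerical assumption. It follows from the order given in the Abstract, Section 3.2 and Section 3.7.3.

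The size and the net direction are unknown. The move from 0.35 to 0.42 against experts, and from 0.25 to 0.36 within the group, shows what a 5-point practice gain could do with no AI effect at all. It rests on assumed accuracies of 0.75, 0.80 and 0.85, 50% prevalence, a binary item and independent errors, none of which comes from the protocol. It is neither a forecast nor evidence that the AI program is without effect.

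**What to change.** **If reading has not begun**

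- Split the 100 films at random into sets A and B of 50, with the same split for all three non-experts.
- Session 1: read set A unaided and set B with AI. Session 2, about a month later: swap, with the films re-ordered.
- Compute the planned kappas within each set-by-session cell, and average the AI-minus-unaided difference over the two sessions.

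This keeps 3 readers, 100 films and 600 readings. The costs to state are:

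- The AI program must be ready at session 1.
- AI landmarks may carry over to later unaided reads, of the same films and of others. The swap cancels an additive session effect but not this.
- Half the unaided reads move to session 2, so the unaided expert-versus-non-expert comparison should use, or also report, session 1 reads.
- Each kappa rests on 50 films instead of 100, so single cells are less precise.

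**If the order is kept or reading has begun**

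- In Section 3.2, replace the statement that the interval prevents learning effects with one that it limits recall.
- Report and interpret the change as the effect of AI plus a second reading, not of AI alone, and word the Discussion to match.

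This second route costs only wording, but the AI effect stays unidentified.

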### Inclusion and exclusion criteria

3.3

Inclusion criteria

1.Adult male or female aged 20 to 60 years2.Ability to understand the study protocol and agrees to participation, and who voluntarily signs the institute review board (IRB)-approved consent form3.No communication problems during the physical examination and X-ray test

Exclusion criteria

1.Past trauma or surgery that may induce a structural problem in the lumbar spine (e.g., osteoporosis, fracture, and lumbar spine surgery)2.A history of disease that may induce a structural change in the lumbar spine (e.g., congenital spinal deformity, ankylosing spondylitis, idiopathic scoliosis, and tumor)3.An obesity factor of mid to high severity based on BMI (>30 kg/m^2^) that prevents manual spinal diagnosis4.A history of psychotic disorder, alcohol addiction, or drug addiction5.Pregnant mothers or women planning pregnancy6.Other individuals deemed unsuitable for the study by the principal investigator

### Sample size calculation

3.4

As this study is an exploratory clinical study, it was deemed unnecessary to calculate the sample size using the standard formula. The guideline of the evaluation of clinical effectiveness of AI-based medical devices (Ministry of Food and Drug Safety, South Korea, 2019) suggests that, for cases where the sample size cannot be estimated using a statistical method, the required number of subjects may be calculated in reference to relevant data (e.g., a published clinical study, etc.).^[12]^ The estimated number of subjects was 100 based on a review of previous studies related to this 1;

1.a study by Lee et al that analyzed the concordance between the CMT manual diagnosis and radiological diagnosis (n = 22)^[13]^;2.a study that compared the results of expert/non-expert/AI diagnosis of spinal alignment using X-ray images (n = 35)^[14]^;3.a study that compared the X-ray angles between experts and non-experts to test a program that automatically detects the Cobb's angle in scoliosis.^[15]^

